### Study population

All willing patients who meet age, Tanner stage and BMI criteria, and have participated for at least 12 months in a lifestyle intervention program, will be offered formal assessment for study inclusion. Patients who continue to meet eligibility criteria will be invited to be included in the trial.

#### Inclusion criteria

(i)Completed a minimum of 12 months in multidisciplinary lifestyle intervention and/or pharmacotherapy weight loss program;(ii)Consensus in the multidisciplinary child obesity team on the diagnosis of suboptimal outcome (defined as a TBW loss of < 10% after 12 months) following multidisciplinary lifestyle interventions;(iii)Age 13–17 years;(iv)Severe obesity meeting International Federation for the Surgery of Obesity and metabolic disorders (IFSO) criteria for bariatric surgery: BMI ≥40 kg/m^2^ with minor comorbidities, or BMI ≥35 kg/m^2^ with at least one major comorbidity, corrected for age and sex according to the International Obesity Task Force (IOTF) criteria.(v)Tanner stage ≥IV;(vi)Consensus in the multidisciplinary child obesity team, during the multidisciplinary meeting, on a motivated participation during the lifestyle intervention program so far, likely to persist in the future. The participant must demonstrate commitment to a bariatric program in the knowledge that they will be expected to continue with this effort after the bariatric surgery;

#### Exclusion criteria

(i)Unable to consent as appropriate;(ii)Illiteracy (inability to read and understand questionnaires);(iii)Secondary obesity – obesity caused by a uncontrolled medical condition;(iv)Known syndrome or genetic disorder (such as Prader-Willi syndrome);(v)Skeletal immaturity (Tanner stage ≤III) – pre-menarche – bone age < 15 years in boys;(vi)Ongoing addiction (alcohol, drugs, medication);(vii)Previous bariatric, gastro-esophageal reflux or gastric surgery;(viii)Uncontrolled psychiatric disorder;(ix)Inflammatory bowel disease;(x)Non-support of both parents / caregivers.

### Eligibility criteria study centers and bariatric surgeons

Surgical sites are required to have (i) a bariatric team performing at least 300 adult bariatric procedures yearly, (ii) an existing child obesity management program, or a close link with such a program in another institute and (iii) an intensive care unit that treats adolescents, or access to such a facility nearby.

The bariatric surgeon(s) will be required to have a minimum experience of at least fifty of each bariatric procedure (SG and RYGB) in adults.

### Intervention

Eligible participants will be randomized to receive either RYGB or SG (both in combination with lifestyle intervention). To assure high quality of both bariatric procedures surgical protocols have been written and will be monitored during the trial.

All patients included in the study will have a protein diet (Modifast or Weight care) 2 weeks prior the surgery, with a standard number of calories per day (approximately 600 cal). This very low-calorie diet is given in order to decrease liver volume and increase laparoscopic workspace. It is proven that this very low-calorie diet reduces the postoperative complication rate in patients who underwent a laparoscopic RYGB [21].

Patients are required to take vitamins daily for the rest of their life (including extra Calcium+ Vitamin D, Vitamin B12 and Iron) according to local guidelines.

#### Laparoscopic RYGB

The surgical procedure has been described earlier by Dillemans et al. (circular anastomosis) [22] and by Lönroth et al. (linear anastomosis) [23]. In short, after induction of pneumoperitoneum and placement of five laparoscopic ports the majority of the stomach is disconnected from the normal digestive route using a linear stapler to leave a small (20–25 ml) gastric pouch in continuity with the esophagus. The jejunum is transected approximately 100 cm (cm) from the ligament of Treitz and the distal end (Roux limb) is anastomosed to the gastric pouch, as a gastrojejunal anastomosis, using a 25 mm circular stapler or a 30–45 mm linear stapler. Thereafter, the proximal end (the biliary limb) is attached approximately 50–150 cm distally along the jejunum, as a jejuno-jejunal anastomosis. Furthermore, the mesenteric defects beneath the jejunojejunostomy and at Petersen’s space will be closed. Before closure of the skin incisions, the gastrojejunostomy is tested for leakage using methylene blue and an easy flow drain (optional) will be placed. After closure of the incisions bupivacaine will be injected subcutaneously.

#### Laparoscopic SG

The procedure was performed by Gagner [24]. SG involves the excision of the majority of the stomach on its greater curvature side, using a stapling device. In short, pneumoperitoneum is induced with the Verres needle and five laparoscopic ports are placed, as with the laparoscopic RYGB. The resection line begins from approximately five centimeters proximal to the pylorus, proceeding to the angle of His to result in a tube or sleeve-shaped remnant stomach of approximately 25% its original capacity. A calibration bougie, usually sized between 34 and 40 Fr, is used to standardize the sleeve size. Before closure, the stomach remnant will first be removed and the gastric tube will be tested for leakage with methylene blue. Furthermore, after closure of the incisions bupivacaine will be injected subcutaneously. Placement of an easy flow drain is optional.

### Outcomes

#### Primary outcome measure (non-inferiority)

The proportion of patients that achieve a TBW loss of at least 20% at 3 years after surgery.

#### Secondary outcome measures

To compare outcomes between SG and RYGB. In addition, a historical cohort of adolescents who participated in a lifestyle intervention program only will be compared to both study arms on these secondary objectives (except for (ii) and (vii)).
(i)BMI, BMI standard deviation score and TBW loss [1, 3 and 5 years after the bariatric surgery]: weight loss is measured in kilogram and as percentage TBW loss;(ii)Adverse health events [1, 3 and 5 years after the bariatric surgery]: including complications (within 30 days and beyond 30 days of bariatric procedure) and the need for re-operation. Complications will be scored according to the Clavien Dindo Classification [25];(iii)Resolution of co-morbidities [1, 3 and 5 years after the bariatric surgery]: blood pressure (systolic and diastolic), lipid profile (HDL, LDL, TG), glucose control (HbA1c, fasting blood glucose level, fasting insulin, HOMA-IR), Obstructive Sleep Apnea (OSA) (Epworth sleepiness scale), kidney function (Glomerular Filtration Rate, microalbuminuria, creatinine), liver disease (i.e. non-alcoholic fatty liver disease) (alkaline phosphatase, gamma glutamyl transpeptidase, aspartate-aminotransferase, alanine-aminotransferase, bilirubin, ultrasound (baseline, 3 and 5 years post-surgery) and decrease/change in medication for each of the co-morbidities;(iv)Resolution of OSA, T2D and pre-diabetes, hypertension, dyslipidemia, deranged liver function [1, 3 and 5 years after the bariatric surgery];(v)Prevalence of cardio-metabolic risk factor measures [1, 3 and 5 years after the bariatric surgery];(vi)Routine post-bariatric surgery nutritional blood tests at each assessment [1, 3 and 5 years after the bariatric surgery]: including full blood count, electrolytes, creatinine, fasting glucose, fasting insulin, HbA1c, liver parameters and function tests, iron, ferritin, vitamin B12, thiamine, folate/red cell folate, lipid profile, 25-hydroxyvitamin D, calcium and parathyroid hormone;(vii)Bone health measures and the incidence of bone fractures [baseline and at 2 and 5 years after the bariatric surgery]: bone mineral density (DEXA-scan), osteocalcin, PINP, CTX and bone-specific alkaline phosphatase;(viii)Generic and obesity-specific health-related quality of life [1, 3 and 5 years after the bariatric surgery]: IWQOL-Lite, RAND-36, Kidscreen-27;(ix)Psychosocial health measures and educational attainment [1, 3 and 5 years after the bariatric surgery]: education, depression (Beck Depression Inventory), anxiety (Beck Anxiety Inventory), self-esteem (Kidscreen-27, IWQOL-Lite), attention deficit hyperactivity disorder (AVL);(x)Patient satisfaction [1, 3 and 5 years after the bariatric surgery]: single question scale 1–10 and net promotor score;(xi)Body composition [1, 3 and 5 years after the bariatric surgery]: DEXA-scan.

### Sample size calculation

A clinical successful weight loss is defined as a TBW loss of ≥20% for this study. We obtained unpublished summary statistics from the Teen-LABS study group, which were used to inform the power calculation. The proportion of participants losing at least 20% of their total body weight at 3 years in the Teen-LABS study was 63% after SG and 72% after RYGB.

The power calculation requires the estimation of two parameters, i.e. the mean TBW loss of participants at 3 years and the difference in mean TBW loss that would be considered clinically important (the non-inferiority margin). The hypothesis is that 70% of the participants will achieve a TBW loss of 20%. The non-inferiority margin was chosen on the basis of the opinions of the clinical applicants and was set at 20%.

A group sample size of 132 patients/arm, allowing for a 15% dropout, is needed to achieve 90% power to detect non-inferiority using a one-sided Z-test (unpooled). The non-inferiority margin is − 0.20000. The true difference between the means is assumed to be 0. The significance level (alpha) of the test is 0.02500.

### Randomization

Randomization will be performed by the coordinating investigator after trial eligibility and informed consent to participate in the trial have been confirmed. Randomization will be performed using a computerized randomization program (Research Manager), which will produce unchangeable computer-generated numbers. Randomization will be stratified according to centers in order to ensure balanced groups. Randomization will be on a 1:1 basis using block sizes of 6–8 participants.

### Blinding

Patients and caregivers (but not the surgical team) will be blinded to which procedure was performed until the two-month follow-up visit, which gives unbiased data regarding the 30-day complications. Standardized management, appropriate to both SG and RYGB, will be conducted during the blinded period and dietary advice and supplementation appropriate to both procedures will be administered to all patients.

Within the first 2 months, the trial code will only be broken in exceptional circumstances when knowledge of the surgical technique is essential for the safety of the patient. If unblinding is required, a formal request for unblinding must be made. The principle investigator (PI) will enter Research Manager for unblinding and will contact the holder of the code break list as a back-up. The coordinating investigator will notify the Sponsor in writing as soon as possible following the code break including the reason(s) for the code break.

### Data collection, data management and data analysis

After written informed consent is obtained, all patients will be assigned a study number. This moment is defined as baseline; the date when the participant is examined and found suitable to be randomized. Data will be pseudonymous inserted into a computerized database, Research Manager Software (certified by the ‘Information Security Management System 27001’), by local investigators. All data will be handled confidentially, anonymously and in accordance with the international accepted Personal Data Protection Act. A subject identification list will be drafted. This list will be password protected. The subject identification list and the password will be administered by the coordinating and principal investigator.

The follow-up of patients that withdrew from the study will continue according to the implemented standard care for adults who underwent bariatric surgery. This actually means that the follow-up just continues according to the follow-up schedule of the study, because the follow-up in the study is according to the standard care (including laboratory assays and quality of life assessment) for adults.

Primary analyses will be based on intention-to-treat and will include all randomized patients. In addition, a per-protocol analysis will be performed to explore the influence of protocol deviations and compare the results with the primary analysis. Furthermore, to explore the influence of contamination (switching between study arms) we will perform an as-treated analysis, the results of which will be compared with the results of the primary analysis.

The primary parameter, the proportion of patients achieving at least 20% TBW loss at 3 years, will be compared using descriptive statistics and a logistic regression analysis.

Secondary parameters, including quality of life questionnaire scores and other continuous outcomes measured at multiple time points, will be compared using a mixed regression model with baseline and post-surgery measures modeled jointly. Changes in treatment effect with time will be assessed by adding a treatment by time interaction to the model and comparing models using a likelihood ratio test. Time to event outcomes will be compared using survival methods for interval censored data. Frequencies of adverse events will be described. Treatment differences will be reported with 95% confidence intervals (CIs). A detailed analysis plan will be prepared during the feasibility phase 1.

We will compare outcomes between groups at the end of phase 1. Other interim analyses will be decided in discussion with the data safety monitoring committee (DSMC).

In addition, one subgroup analysis is planned; outcomes will be described for male and female participants. Differences in treatment effect between the two subgroups will be tested by including interaction terms to the analysis model.

Missing data will be excluded and will not be imputed. To address possible bias of the missing values, the baseline characteristics of patients with and without missing values will be compared. We will do our utmost to collect outcome measures wherever possible to minimize the number of missing values. This means we will also accept patient reported weight in case of missing weight data. In addition, we will try to retrieve the reason for the missing value, such as missing because of weight gain.

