A recent systematic review of medium- and long-term outcomes (minimum three-year follow-up) of bariatric surgery including 950 adolescents with severe obesity, aged twelve to nineteen years, showed an average decrease in BMI of 13.3 kg/m^2^. Resolution of T2D/insulin resistance, hypertension and dyslipidemia occurred in 69.9, 61.6 and 57.1% of patients respectively. The rate of reoperation was 9.6%, mostly because of postoperative complications and suboptimal weight loss [16]. Olbers et al. reported similar weight loss results over 5 years among adolescents and adults who received a Roux-en-Y gastric bypass (RYGB), with a mean BMI-reduction of 13.1 kg/m^2^ in the adolescent intervention group. Notably, the control group of adolescents, who attended multimodal lifestyle intervention programs, experienced a mean increase in BMI of 3.3 kg/m^2^ across the five-year study period. Regarding comorbidities among adolescents who received the RYGB, resolution of hypertension was seen in 100%, resolution of dyslipidemia in 82.7% and complete resolution of T2D and disturbed glucose homeostasis in 100% (*n* = 3) and 85.7%, respectively [17]. In recent years, Inge et al. have published three-year outcomes from the Teenage Longitudinal Assessment of Bariatric Surgery (Teen-LABS) prospective longitudinal study including adolescents undergoing sleeve gastrectomy (SG) and RYGB. This study showed a mean three-year BMI reduction of 15 kg/m^2^ after RYGB and 13 kg/m^2^ after SG. Furthermore, significant improvements were observed in weight related quality of life and cardio-metabolic health (95% remission of T2D, 86% remission of abnormal kidney function, 74% remission of elevated blood pressure, 76% remission of prediabetes and 66% remission of dyslipidemia). This study suggested that risks associated with the procedures may be more prevalent after RYGB and included specific micronutrient deficiencies and the need for additional abdominal procedures [18]. The Teen-LABS group subsequently published 5-year outcomes after RYGB in comparison to adults in a similar study, LABS (Longitudinal Assessment of Bariatric Surgery). This confirmed similar weight loss outcomes between adolescents and adults, but a more favorable T2D and hypertension outcome in adolescents, supporting the case for early intervention [19].

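### The primary endpoint does not exclude success reached through a second bariatric operation, and only the intention-to-treat result decides non-inferiority, so a converted sleeve can count as a sleeve success

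*Protocol article*

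**What the plan says.** All statements are in the protocol article.

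- **Analysis sets** (Data collection, data management and data analysis): "Primary analyses will be based on intention-to-treat and will include all randomized patients". Two further analyses are planned and serve only for comparison with that result. On deviations, the article says that "a per-protocol analysis will be performed to explore the influence of protocol deviations". On patients who change arms, it says that "to explore the influence of contamination (switching between study arms) we will perform an as-treated analysis". Nothing says what follows if the three disagree.
- **Primary endpoint** (Primary outcome measure): "The proportion of patients that achieve a TBW loss of at least 20% at 3 years after surgery". There is no condition on how the loss was reached.
- **Reoperation** (Secondary outcome measures, item ii) is collected among adverse health events, "including complications (within 30 days and beyond 30 days of bariatric procedure) and the need for re-operation", at 1, 3 and 5 years. It is not linked to the primary endpoint.
- **Hypothesis**: the claim concerns SG plus lifestyle intervention against Roux-en-Y gastric bypass (RYGB) plus lifestyle intervention.
- **Background**: a systematic review of bariatric surgery in adolescents found 9.6% reoperation, "mostly because of postoperative complications and suboptimal weight loss".
- **Sample size calculation**: 70% success in both arms, margin 0.20, one-sided alpha 0.025, unpooled Z-test, 90% power, 15% dropout, 132 per arm.

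**The concern.** In a superiority trial, departures from the assigned treatment usually dilute the difference and make intention-to-treat cautious. In a non-inferiority trial the same dilution helps the claim. Two separate mechanisms are in play.

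1. **Rescue after the index operation.** A sleeve that gives too little weight loss is revised or converted, the patient reaches 20% by year 3, and the success is credited to SG. The result then describes SG with later revision when needed, while the hypothesis speaks of SG with lifestyle intervention.
2. **Crossover at the index operation.** Patients who receive the other procedure are analysed as randomized, and the two arms move towards each other.

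Either mechanism could let SG be declared non-inferior when SG by itself is worse by the full margin. The article names contamination as something to explore but gives that analysis no part in the decision.

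**Working it through.** **Reproducing the plan's figure.** n per arm = (1.960 + 1.282)² × 2 × 0.70 × 0.30 / 0.20² = 110.3, so 111. Allowing for 15% dropout, 111 / 0.85 = 130.6, so 131, against the stated 132. Evaluable per arm: 132 × 0.85 = 112. Power at 112 is 90.4%. The sample size is not in dispute.

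**False-claim rate.** Let d be the expected SG minus RYGB difference in scored success. Then

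P(non-inferiority claimed) = Φ((d + 0.20)/SE − 1.96), with SE = √[p_SG(1 − p_SG)/112 + p_RYGB(1 − p_RYGB)/112].

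The starting point is exactly at the margin: RYGB 70% (planning value) and SG without rescue 50%. Then d = −0.20, SE = 0.0641 and the rate is 2.5%.

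**Rescue.** Assume a share c of SG patients is converted, that all of them would otherwise have failed, and that a share s of them then reaches 20%. Scored SG success becomes 0.50 + c × s. The last column adds half that gain to RYGB. Both c and s are assumptions.

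| c | s | gain c × s | SG only rescued | RYGB gains half as much |
|---|---|---|---|---|
| 2% | 40% | 0.008 | 3.3% | 2.9% |
| 2% | 60% | 0.012 | 3.8% | 3.1% |
| 5% | 40% | 0.020 | 5.0% | 3.6% |
| 5% | 60% | 0.030 | 6.8% | 4.2% |
| 10% | 40% | 0.040 | 9.1% | 5.0% |
| 10% | 60% | 0.060 | 15.4% | 6.9% |

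Worked example, last row: p_SG = 0.56, d = −0.14, SE = 0.0638, so Φ(0.06/0.0638 − 1.96) = Φ(−1.02) = 15.4%. If both arms gain equally, d stays at −0.20 and the rate stays at 2.5%.

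**Crossover.** If 5% of each arm receives the other procedure, the expected rates are 0.95 × 0.50 + 0.05 × 0.70 = 0.51 and 0.95 × 0.70 + 0.05 × 0.50 = 0.69. The false-claim rate is then 5.0%. At 10% the rates are 0.52 and 0.68, and the false-claim rate is 9.0%. These shares are also assumptions.

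**Would a per-protocol set cure rescue?** Not if it drops converted sleeves. On the assumption above, those patients are all failures of SG alone, so dropping them raises SG success.

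- 5% dropped: 0.50/0.95 = 0.526 with 106.4 SG patients, false-claim rate 6.0%.
- 10% dropped: 0.50/0.90 = 0.556 with 100.8 SG patients, false-claim rate 13.2%.

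Rescue is therefore a matter of how the endpoint is defined. The choice of analysis set bears on crossover.

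**The case against.** - **No rule on revision is stated.** A reader might infer that the protocol counts revisional surgery to the original arm. No sentence says so; it follows only from intention-to-treat combined with an endpoint that ignores revision. The article defers to a detailed analysis plan that is not shown and may settle this. That stands as a limit. It does not remove the point, because the endpoint and the exploratory status of the other analyses are fixed in print.
- **The plan is not blind to deviations.** A reader might infer that intention-to-treat is the only analysis, or that the others count for nothing. That goes too far: two further analyses are planned and compared with the primary one, and one is aimed at switching. What is missing is any stated consequence of a disagreement. Whether per-protocol should share in the decision is itself debated.
- **Comparing strategies as randomized is legitimate.** The stated objective is guidance on procedure choice, and reoperation is reported separately. This supports keeping that result in view. It fits less well as the sole basis for a hypothesis about SG with lifestyle intervention.
- **The sizes are assumption-driven.** The 9.6% covers all procedures and all causes, so it cannot be read as an SG conversion rate. The Background even suggests that additional abdominal procedures may be more common after RYGB. Rescue in both arms shrinks or removes the effect. Blinding patients and caregivers until two months also limits patient-driven crossover at the index operation. All of this stands, and the size is therefore given as a range.

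**Conclusion.** The concern holds in a limited form. As written, an SG patient converted before year 3 can be scored as an SG success, and no planned analysis outside intention-to-treat bears on the claim. The direction favours non-inferiority whenever rescued successes are more frequent after SG than after RYGB.

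On the assumed inputs, the 2.5% error rate becomes 3.3% to 15.4% with SG-only rescue, 2.9% to 6.9% if RYGB gains half as much, and is unchanged if the gains are equal. Two-way crossover of 5% to 10% gives 5.0% to 9.0%. The results rest on a true 50% against 70%, 112 evaluable per arm, and converted sleeves that would otherwise all have failed. The documents supply no conversion or crossover rate by arm, so none of these figures predicts what this trial will see.

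**What to change.** 1. **Endpoint.** In the primary analysis, score a second weight-loss bariatric procedure (revision or conversion) before the 3-year assessment as not achieving the endpoint, in both arms. The information comes from item ii of the secondary outcomes, "the need for re-operation", provided the type and reason of each reoperation are recorded.
2. **Sensitivity analysis.** Keep the result that ignores reoperation, analysed as randomized, and report it beside the primary one.
3. **Crossover.** State that the non-inferiority claim also needs a per-protocol result consistent with the −0.20 margin. Patients converted later stay in that set as failures and are not excluded.
4. **Borderline cases.** Prespecify how to score an operation done for a complication in a patient with good weight loss.

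This is protocol and analysis-plan wording. It changes scoring only, not patient care. The cost is a lower chance of meeting the criterion. As an illustration, suppose the planned 70% includes 2 points of rescued success. If these are lost in both arms (68% each), the formula above gives power of 89.4% instead of 90.4%. If they are lost in SG only (68% against 70%), it gives 83.0%. Requiring per-protocol support lowers the chance somewhat further.

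### The as-treated check on switching is supportive only, and its gap from intention-to-treat does not reliably show what switching did to the non-inferiority result; a complier-average estimate should be added

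*Protocol article*

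**What the plan says.** In the Protocol article, section Data collection, data management and data analysis, the primary analysis is by intention-to-treat in all randomised patients. Two further analyses follow. A per-protocol analysis explores protocol deviations. The other is aimed at switching: "to explore the influence of contamination (switching between study arms) we will perform an as-treated analysis". Its findings are then to be set beside the intention-to-treat findings.

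The same section says that a detailed analysis plan will be prepared during the feasibility phase; that plan is not shown. The article gives no expected switching rate, direction or reasons.

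The section Sample size calculation fixes the scale on which any such result would be read: "The non-inferiority margin is − 0.20000", with an assumed 70% success rate and no true difference. The test is a one-sided unpooled Z-test, and "The significance level (alpha) of the test is 0.02500".

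**The concern.** The article states a purpose (what switching did to the result) and a method (as-treated set beside intention-to-treat). The two fit only under conditions that the method cannot check.

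If patients who receive the other operation differ in prognosis from the rest, regrouping them moves the as-treated difference even when the operations are equally effective. A gap from intention-to-treat can then reflect who switched, and the absence of a gap can hide real dilution.

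This deserves attention in a non-inferiority trial because switching pulls the randomised arms together, which favours the claim. A check on switching should show that dilution and not add an error of its own. The per-protocol analysis does not fill this role, as it is open to the same kind of selection.

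**Working it through.** **Inputs from the article.** Success 70%, margin 0.20, one-sided alpha 0.025, power 90%, 132 per arm including 15% dropout.

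**The plan's own figure.** n = (1.960 + 1.282)² × 2 × 0.70 × 0.30 / 0.20² = 110.3, so 111 per arm. 111/0.85 = 130.6, so 131; starting from 112, 112/0.85 = 131.8, so 132. The stated size reproduces and is not in dispute. I use 112 evaluable patients per arm below.

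**Assumptions, none of them in the article.** A fraction s of patients randomised to SG receive RYGB instead. Their success under RYGB is q, against p = 70% overall. The true difference (SG minus RYGB) is d, the same in switchers and non-switchers.

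**Formulas.**
- RYGB success in non-switchers: (p − sq)/(1 − s).
- Intention-to-treat difference: d(1 − s), so its error is s|d|.
- As-treated difference: [(p − sq)/(1 − s) + d] − (p + sq)/(1 + s), which simplifies to d + 2s(p − q)/(1 − s²).
- Complier-average estimate: d(1 − s)/(1 − s) = d.

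The last term of the as-treated formula is pure selection. It vanishes only if s = 0 or q = p.

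**No true difference (d = 0).** Intention-to-treat is 0 throughout, so switching has done nothing. As-treated, in percentage points:

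| s | q = 50% | 60% | 70% | 80% | 90% |
|---|---|---|---|---|---|
| 5% | +2.0 | +1.0 | 0 | −1.0 | −2.0 |
| 10% | +4.0 | +2.0 | 0 | −2.0 | −4.0 |

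At s = 2% and q = 50% or 90% the error is 0.8 points. The per-protocol error at s = 10% is about half the as-treated one (±2.2 against ±4.0 points).

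**SG truly at the margin (d = −20 points).**

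| s | Intention-to-treat | As-treated, q = 50% / 70% / 90% | Complier-average |
|---|---|---|---|
| 5% | −19.0 | −18.0 / −20.0 / −22.0 | −20.0 |
| 10% | −18.0 | −16.0 / −20.0 / −24.0 | −20.0 |

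As-treated is further from the truth than intention-to-treat when 2|p − q|/(1 − s²) exceeds |d|. Here that means switchers whose prognosis differs from average by more than about 10 points.

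**False-claim rates at s = 10%, d = −20 points** (normal approximation).
- Intention-to-treat: standard error √[(0.52×0.48 + 0.70×0.30)/112] = 0.0641; excess over the margin 0.02/0.0641 = 0.31; P(Z > 1.96 − 0.31) = 5.0%.
- As-treated, q = 50%: groups of 100.8 (52.2% success) and 123.2 (68.2%); standard error 0.0651; 0.0404/0.0651 = 0.62; P(Z > 1.34) = 9.0%.
- As-treated, q = 90%: groups with 47.8% and 71.8% success; standard error 0.0642; −0.0404/0.0642 = −0.63; P(Z > 2.59) = 0.5%.
- Complier-average: centred on −0.20, so nominally 2.5%.

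Simulation of the same settings agrees: 5.0%, about 9%, 0.5%, and between 2.3% and 2.5% for the complier-average estimate.

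**Balanced switching.** With 5% switching each way, d = −20 points and switchers alike in both directions, intention-to-treat is 51% − 69% = −18 points. As-treated is −20, because the selection terms cancel. The complier-average estimate is −18/0.90 = −20.

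**The case against.** The strongest reply is that nothing is decided by this analysis. Intention-to-treat is primary, as-treated is presented as exploration, and no figure, margin or decision rule depends on it. Because intention-to-treat can be diluted, a supportive analysis by treatment received is a usual companion in a non-inferiority trial. All of this stands, and it limits the point to a minor one.

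A reader might infer that an as-treated analysis can never show the effect of switching. The working does not support that. With balanced switching, or switchers of average prognosis, the planned comparison (−20 against −18 or −19) shows the dilution correctly. At 2% to 5% one-way switching the error is about 1 to 2 points, small against a 20-point margin and against a standard error of √(0.42/112) = 6.1 points.

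A reader might also set the as-treated error against the room in the primary test: at 70% success the half-width is 1.96 × 6.1 = 12.0 points, so the estimate must exceed about −8.0. That room belongs to the intention-to-treat decision, which as-treated error does not touch.

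The article does not say that switching will be frequent or related to prognosis. Patients and caregivers are blinded to the procedure until the two-month visit, which limits patient-driven switching at the first operation; the surgical team is not blinded.

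Finally, the analysis plan that is not shown may contain a randomisation-based estimate and a table of switches with reasons. Their absence from an article is no fault. What remains is that the article itself ties this purpose to this method, and the fit is conditional.

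**Conclusion.** The point holds in a limited form. The as-treated analysis is a legitimate supportive check, but its gap from intention-to-treat is not a reliable measure of what switching did. Under selective one-way switching it errs in either direction: by 1 to 2 points at 5% when switchers' success differs from average by 10 to 20 points, and by about 4 points at 10% when it differs by 20.

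In the least favourable case examined (10% switching by poor-prognosis patients, SG truly at the margin), as-treated reads −16 where intention-to-treat reads −18 and the truth is −20. A reader comparing the two would conclude that switching had made SG look worse, when it had made SG look better.

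These sizes rest on assumed switching rates, on assumed switcher prognosis, and on an effect that is the same in switchers and non-switchers. Severity is minor: a cheap improvement that leaves the primary analysis and the sample size as they are.

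**What to change.** Keep intention-to-treat as primary. For the stated purpose of exploring contamination, add a complier-average (instrumental-variable) analysis with randomised arm as instrument: the intention-to-treat difference in proportions divided by the between-arm difference in the proportion receiving SG as first operation. Give its 95% confidence interval and read it against the −0.20 margin as a supportive analysis. Specifying the first operation keeps later conversions, which may follow from poor weight loss, out of the definition of switching. Label any as-treated result descriptive; it need not be removed.

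The cost is one or two sentences and one simple analysis on the operation received and the primary outcome, which an as-treated analysis needs in any case. The interval is somewhat wider: roughly 1/0.95 = 1.05 times at 5% switching and 1/0.90 = 1.11 times at 10%. The estimate applies to patients who would receive whichever operation they were allocated. It assumes that allocation affects weight only through the operation received and that there are no defiers. Neither assumption can be verified from the data, so both should be stated.
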